### Secondary Outcome Measures

1. **Prevalence of *P. falciparum* malaria at delivery by microscopy**

This outcome measure will be analysed in women in whom blood films (peripheral and/or placental) are collected at delivery.

1. **Prevalence of *P. falciparum* malaria at delivery by histology**

This outcome measure will be analysed in all women from whom an assessable placental biopsy is collected at delivery.

1. **Maternal Hb at delivery by histology**

This outcome measure will be analysed in all women from whom an Hb measurement at delivery is available.

1. **Incidence of symptomatic malaria**This outcome will be analysed in all women that have had 1 IPTp treatment
2. **Prevalence of STIs on Vaginal swab at 28-34 weeks gestation**

This outcome measure will be analysed in all women in whom an assessable swab is collected at 28-34 weeks. Rates of carriage of N gonorrhoeae, C trachomatis and T vaginalis (assessed by PCR) will be compared between groups.

1. **Maternal, perinatal and infant mortality rates**

All deaths, irrespective of cause of death, occurring in the cohort of pregnant women and their fetuses or children between Enrolment and Final Evaluation Visit (6 weeks post partum for pregnant women, deaths from 22 weeks gestation to 28 days post partum for perinatal mortality, deaths from day 28 of life to 12 months of age for infants) will be considered for this analysis

1. **Reported side effects / Adverse events**

All reported side effects following IPTp treatment, irrespective of total number of treatments a woman received, will be considered for these analyses.

1. **Molecular markers of SP resistance**

This endpoint will be assessed in a random sample of PCR-positive samples collected at 2nd treatment and at delivery.

## Sample Size Considerations

The primary objective of the study is to determine the effect of IPTp with SP/AZ compared to SP/CQ clearance treatment on prevalence of low birth weight (LBW) in women using ITNs. The overall power and sample size calculations are thus based on this outcome.

The analyses for this primary outcome measure will use Poisson regression (with or without random effects). Sample size calculations for these types of analyses are non-trivial and often require extensive simulations. For that reason we are using an approximate sample size calculation based on comparison of two Poisson rates.

**Table 3**: Sample size calculations for principal outcomes using appropriate two sided tests, a significance level of 5% and a power of 80%.

|  |  |  |  |  |
| --- | --- | --- | --- | --- |
| **End points** | **Expected Outcomes** | |  | **Sample Size** |
|  | Control | AZ-SP |  |  |
|  |  |  |  |  |
|  |  |  |  |  |
| **Primary** |  |  |  |  |
| Prevalence of LBW | 12% | 8.4% |  | 1163 |
| Mean birth weight | 2.94kg | 3.01kg |  | 970 |
|  |  |  |  |  |
| **Secondary** |  |  |  |  |
| Prevalence of *P. falciparum* at delivery (peripheral & placental) by PCR | 30% | 20% |  | 389 |
| Prevalence of malaria in placental histology | 30% | 20% |  | 389 |
| Mean Hemoglobin at delivery | 10.0 | 10.3 |  | 845 |
| Prevalence of bacterial STI at 2nd/final treatment time point | 30% | 10% |  | 72 |
|  |  |  |  |  |

Previous studies suggest that IPTp with SP can increase birth weight by approximately 130 g. ITNs increase birth weight by around 60 g. The effect of adding SP to ITNs is not clear, but we assume that it increases mean birth weight by approximately 70 g. LBW is seen in 16% of babies born to women not using ITNs in PNG. If ITNs decrease LBW by 25% then we will expect 12% of babies to be LBW. SP+AZ may have additional benefits (through control of STIs which impair fetal growth) over SP alone. Our conservative estimate is that SP + AZ will decrease LBW prevalence by 30%. Based on these assumptions, a sample size of 1,163 and 970 women per arm, respectively, are required to find a 30% reduction in LBW and a 70g increase in birth weight with a power of 80% (Table 3).

Assuming, a loss of 20% during follow-up, we will thus enroll 1396 women per arm.

Assuming that 40% of women have malaria on histology and that the introduction of ITN will decrease this by 25%, we expect a prevalence of malaria on histology of 30%. Based on this assumption and an expectation to collect a good quality placental specimen from 60% of all enrolled women, the chosen sample size is sufficient to detect a 29% reduction in prevalence of malaria histology in women receiving IPTp AZ-SP with a power of 80%(two sided test). This sample size will also be sufficient to detect a 22% reduction in *P. falciparum* prevalence at delivery, a reduction in prevalence of STIs from 25% to 20% and/or a 0.26g/dl increase in maternal Hb with a power of 80%.

An interim analysis will be performed when 1400 women enrolled in the study have delivered and had birth weights recorded. Analysis will compare percentage LBW between control and intervention groups.

Sample size calculations were done [STATA](../STATA) 8 software (College Station, TX)

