## Randomisation and Blinding

### Randomisation procedures

Women will be randomized to receive SP/AZ or SP/CQ using concealed allocation. Each treatment will be randomly assigned to 4 different treatment codes, resulting in a total of 8 treatment codes (i.e. A, B, C, D, E, F, G, H). A block randomization procedure will be used, with blocks of 32, each containing 4 women assigned to each treatment code. This will help maintain concealment of allocation from study staff to the greatest extent possible.

In order to facilitate field operations independent randomization lists will be produced for each health centre / hospital. The resulting list will contain 1500 women for Modilon Hospital, 500 for each of the peripheral clinics in Madang Town, 500 each for the two field teams operating in the Madang North Coast (Mugil & Alexishafen HC) and 500 for Yagaum Health Centre. .

The lists will be generated by an independent statistician, and the code will be held by the DSMB.

Administration of second and third treatment doses will be placebo controlled.

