## Analysis Plan

### Primary Outcome Measures

The analyses for the primary outcome measures will use logistic regression. The primary outcome will be defined as number women giving birth to a child with a birth weight of <2500g. These analyses will adjusted for different covariates such as sex, gestation, genotype, bed net use, number of IPTp treatments received, season of delivery (wet vs dry) and site.

Differences in birth weight will be assessed using analyses of variance (ANOVA) and adjusted for the same covariates.

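### The LBW sample size of 1163 per arm does not come from the Poisson method that section 11.2 names, and the binary rows of Table 3 are not on one stated basis

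*Combined protocol and SAP*

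**What the plan says.** Section 11.2 (Sample Size Considerations) bases the overall sample size on LBW. It states: "The analyses for this primary outcome measure will use Poisson regression (with or without random effects". After remarking that sizing for such models is difficult, it adds: "For that reason we are using an approximate sample size calculation based on comparison of two Poisson rates".

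Table 3 has one caption for all rows: "Sample size calculations for principal outcomes using appropriate two sided tests, a significance level of 5% and a power of 80" per cent. Its binary rows are:

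- LBW, 12% versus 8.4%: 1163
- *P. falciparum* at delivery by PCR, 30% versus 20%: 389
- malaria on placental histology, 30% versus 20%: 389
- bacterial STI, 30% versus 10%: 72

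The text below the table confirms that the figures are per arm: "a sample size of 1,163 and 970 women per arm, respectively, are required to find a 30% reduction in LBW". It then allows for 20% loss and arrives at 1396 per arm.

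Section 11.4.1 names a different model: "The analyses for the primary outcome measures will use logistic regression". Section 11.1.2 describes the primary evaluation as a difference between the groups in the proportion of LBW deliveries.

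**The concern.** The sample size for the primary outcome is the figure that a reader most needs to reproduce. Section 11.2 gives the inputs and names the method, but putting the inputs into that method does not return 1163. The formula that does return 1163 does not return 389 for the malaria rows. Nothing in the table signals a change of method between binary outcomes.

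Two things are at stake. First, the plan does not say on what basis the trial has 80% power for LBW, and it names two different primary models. Second, the malaria rows cannot be compared with the LBW row, so Table 3 misstates how much larger than necessary the trial is for those outcomes.

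**Working it through.** **Inputs.** The rates, two-sided 5% level and 80% power come from Table 3. Allocation is 1:1: section 6.3.1 assigns four codes to each treatment and uses blocks "with blocks of 32, each containing 4 women assigned to each treatment code". So z₁ = 1.960, z₂ = 0.842 and (z₁ + z₂)² = 7.849. Write d = p₁ − p₂ and p̄ for the mean of p₁ and p₂.

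**Step 1: reproduce the plan's 1163.** The two-proportion formula with pooled null variance is

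n = [z₁√(2p̄(1−p̄)) + z₂√(p₁(1−p₁) + p₂(1−p₂))]² / d².

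For 0.12 and 0.084 it gives 1108.3, that is 1109. The continuity correction

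n_c = (n/4)·[1 + √(1 + 4/(n·d))]²

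gives 1163.2, which matches the printed figure when rounded to the nearest integer.

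**Step 2: apply the method that the plan names.** Two Poisson rates:

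- rate difference: 7.849 × (0.12 + 0.084) / 0.036² = 1235.5
- square-root scale: 7.849 / [2(√0.12 − √0.084)²] = 1225.8

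These are 1236 and 1226 per arm, 73 and 63 above 1163 (6.3% and 5.4%). Other Poisson variants do not close the gap: the log rate ratio gives 1221 to 1249 and the exact conditional test about 1280. Other binary variants (unpooled, arcsine, log risk ratio, log odds ratio) give 1101 to 1126. Of the formulas tried, only the continuity-corrected one falls within 3% of 1163.

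**Step 3: the other binary rows at 80% power.**

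| Row | Printed | Two proportions, uncorrected | Two proportions, corrected | Poisson, square root | Poisson, difference |
|---|---|---|---|---|---|
| LBW, 12% v 8.4% | 1163 | 1108.3 | 1163.2 | 1225.8 | 1235.5 |
| Malaria rows, 30% v 20% | 389 | 293.2 | 312.8 | 388.5 | 392.4 |
| STI, 30% v 10% | 72 | 61.6 | 71.2 | 73.2 | 78.5 |

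The 389 agrees with the square-root Poisson figure rounded up. It also agrees with an unpooled two-proportion calculation at 90% power: (1.960 + 1.282)² × (0.3×0.7 + 0.2×0.8) / 0.1² = 388.8. It agrees with neither two-proportion figure at 80% power, exceeding 313 by 76 (24%) and 294 by 95 (32%).

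**Step 4: power for two proportions.** Uncorrected power is Φ{[d√n − z₁√(2p̄(1−p̄))] / √(p₁(1−p₁) + p₂(1−p₂))}. With correction, d becomes d − 1/n.

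- n = 1163, uncorrected: (1.2277 − 0.8389)/0.4273 = 0.910, power 81.9%
- n = 1163, corrected: (1.1984 − 0.8389)/0.4273 = 0.841, power 80.0%
- n = 1396 × 0.8 ≈ 1117: 80.3% uncorrected, 78.3% corrected

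**The case against.** The best defence is that only the description is wrong. LBW is binary, sections 11.1.2 and 11.4.1 plan a comparison of proportions by logistic regression, and 1163 per arm is a sound figure for that comparison. The 389 cells do not determine enrolment, they err on the high side, and section 11.2 separately states which effects the chosen sample can detect for histology, *P. falciparum*, STI and haemoglobin. All of that stands, and it limits the consequence.

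The caption's reference to appropriate tests helps less. It can justify a different test for means. It does not explain two bases for binary prevalences, nor a LBW figure that differs from the method named for LBW.

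Three stronger readings are tempting, and the documents do not support them:

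- **That the trial is underpowered.** On the Poisson basis power is 77.6% to 77.9% at 1163 per arm and 75.9% to 76.3% at 1117. But the Poisson variance p exceeds the binomial variance p(1−p), so these figures understate power for comparing two proportions.
- **That the 389 cells are certainly Poisson figures.** The 90% power calculation fits equally well. In that case the cells would contradict the caption's 80%.
- **That the STI row proves a mixture of methods.** Its 72 lies between 71.2 (corrected two proportions) and 73.2 (square-root Poisson). No single rounding rule turns 1163.2 into 1163 and 71.2 into 72. The inconsistency rests on 1163 against 389.

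**Conclusion.** The point holds as an error of description and consistency. The method named in section 11.2 needs 1226 to 1236 per arm where the plan prints 1163, and 1163 is reproduced by two proportions with continuity correction. The two 389 cells cannot come from that formula at the stated 80% power, whatever their origin. The binary rows of Table 3 are therefore not on one stated basis.

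No power shortfall is shown at 1163 evaluable women per arm: power is 80.0% with correction and 81.9% without. After 20% loss from 1396 it is 78.3% or 80.3%, so whether the target is still met depends on a choice that the plan does not state. These figures assume the plan's rates, equal arms and an unadjusted comparison of two proportions. They would not carry over directly to the Poisson regression of section 11.2 with its model-based variance, so the conflict with section 11.4.1 should be settled together with the sample-size text.

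**What to change.** 1. In section 11.2, replace both the sentence naming Poisson regression and the sentence naming two Poisson rates. State that LBW was sized as a comparison of two proportions, consistent with the logistic regression of section 11.4.1.
2. Put every binary row of Table 3 on that method at 80% power and say which version is used:
   - with continuity correction: keep 1163 and 72, and change both 389 cells to 313; or
   - without correction: 1109, 294, 294 and 62.
3. State the power for LBW at about 1117 evaluable women per arm (1396 less 20%): 78.3% with correction or 80.3% without.

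The cost is a few sentences plus two table cells under the corrected option or four under the uncorrected one. Enrolment need not change. On the uncorrected basis, 1109/0.8 = 1387 lies within the planned 1396. On the corrected basis, 1163/0.8 = 1454 exceeds 1396, so keeping 1396 means stating 78.3% openly.

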**Primary Objective**

### Primary Outcome Measure

1. Proportion of infants with birth weight <2500 g.

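### Under approximate normality, the two Table 3 rows for LBW and mean birth weight rest on different birth-weight SDs (about 0.37 kg and 0.55 kg), and neither is stated

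*Combined protocol and SAP*

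**What the plan says.** Table 3 in section 11.2 (Sample Size Considerations) lists two birth-weight rows under its Primary label, calculated "using appropriate two sided tests, a significance level of 5% and a power of 80" per cent:

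- "Prevalence of LBW | 12% | 8.4" per cent, with 1163 per arm;
- "Mean birth weight | 2.94kg | 3.01kg", with 970 per arm.

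The text below the table joins the rows: "a sample size of 1,163 and 970 women per arm, respectively, are required to find a 30% reduction in LBW and a 70g increase". The assumptions have separate origins:

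- **Control LBW rate.** It starts from 16% without nets: "If ITNs decrease LBW by 25% then we will expect 12% of babies to be LBW".
- **LBW effect.** "Our conservative estimate is that SP + AZ will decrease LBW prevalence by 30" per cent, after a remark that STI control may add benefit beyond SP alone.
- **Mean effect.** "The effect of adding SP to ITNs is not clear, but we assume that it increases mean birth weight by approximately 70 g".

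The primary outcome in the Objectives is "Proportion of infants with birth weight <2500 g". Section 11.2 states that overall power and sample size are based on LBW. It gives no birth-weight SD and no distribution.

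**The concern.** Both rows describe the same babies, arms and measurement, and LBW is that measurement cut at 2500 g. Once a mean and an SD are assumed, the proportion below 2500 g is largely determined, so the two rows should agree on one SD. They appear not to. The control-arm part of the mismatch involves no treatment effect at all.

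At stake is whether the planning assumptions can be trusted. A reader cannot tell whether the 12%, the 2.94 kg or the unstated SD is the wrong one. A reader may also take the 70 g gain and the 30% LBW reduction as one expected effect, and suppose that 80% power on the primary follows from the birth-weight gain.

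**Working it through.** **Inputs, from section 11.2 unless noted.** Two-sided 5% and 80% power, so z = 1.960 + 0.842 = 2.802. LBW 12% v 8.4%, 1163 per arm. Means 2.94 v 3.01 kg (difference 0.07 kg), 970 per arm. LBW threshold 2.5 kg (Objectives). Normality is my assumption; the plan states none.

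**1. Reproduce the LBW row.** The two-proportion formula for 0.12 v 0.084 gives about 1,109 per arm uncorrected and 1,163 to 1,164 with continuity correction. The printed 1163 is right for its inputs.

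**2. Find the SD behind 970.** From n = 2(2.802 × SD / 0.07)²:

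SD = 0.07 × √(970/2) / 2.802 = 0.550 kg.

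Forward, SD 0.55 returns 970, 0.54 gives 935 and 0.56 gives 1,005. So 0.55 kg is very probably the value used.

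**3. LBW implied by that SD.**

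- Control: Φ((2.5 − 2.94)/0.55) = Φ(−0.800) = 21.2%, against 12% printed.
- Treated: Φ((2.5 − 3.01)/0.55) = Φ(−0.927) = 17.7%, against 8.4% printed.
- Relative reduction: 1 − 17.7/21.2 = 16.5%, against 30%.

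**4. SD implied by the LBW row at the printed means.**

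- Control: 0.44/1.175 = 0.374 kg. Treated: 0.51/1.379 = 0.370 kg.
- Birth-weight n at 0.374 kg: 2(2.802 × 0.374/0.07)² ≈ 448. At 0.370 kg it is about 439. Call it 440 to 450, against 970.
- At 0.374 kg a 70 g shift takes 12% to about 8.7%, a 28% reduction, so at this SD the two effects nearly agree.

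**5. Other readings of the 970.**

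| Test and power | Implied SD (kg) | Control LBW | LBW reduction |
| --- | --- | --- | --- |
| Two-sided, 90% | 0.476 | 17.7% | 20% |
| One-sided, 80% | 0.62 | 23.9% | 14% |
| One-sided, 90% | 0.527 | 20.2% | 17% |

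None gives 12%.

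**6. Non-normal shapes with mean 2.94 kg and SD 0.55 kg.** Left-skewed (skew-normal) shapes give control LBW of 20 to 21%. Moderate low-weight-tail mixtures give about 16 to 21%. Only extreme tails come near 12%: for example, 5% of babies averaging 1.2 kg gives 12.4%. A uniform 70 g shift never cut LBW by more than about 18% in these shapes.

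**7. LBW power at 1,163 per arm.** The uncorrected two-proportion formula is

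power = Φ{[|p₀ − p₁|√n − 1.960√(2p̄(1 − p̄))] / √(p₀(1 − p₀) + p₁(1 − p₁))}.

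For 12% v 8.4%: (0.036 × 34.10 − 1.960 × 0.428)/0.427 = 0.91, so power is 82% (80% with the continuity correction used for the 1,163).

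| If the effect were a uniform 70 g shift | LBW, control v treated | Power |
| --- | --- | --- |
| SD 0.374 kg | 12.0% v 8.7% | 75% |
| SD 0.55 kg, mean 2.94 kg | 21.2% v 17.7% | 57% |
| SD 0.55 kg, LBW held at 12% | 12.0% v 9.6% | 45% |

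**8. Uniform shift that matches a 30% reduction from 12%.** SD × (1.379 − 1.175) = SD × 0.2037: about 76 g at SD 0.374 kg and 112 g at 0.55 kg.

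**The case against.** **Each row is right on its own inputs.** This stands. The conflict needs a back-solved SD and a distribution that the plan does not state, so it is a conflict between assumptions, not a slip in either calculation.

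**A heavy low-weight tail can reconcile the figures.** Partly true. A control mixture of 94% N(3.045, 0.359) and 6% N(1.3, 0.4) has mean 2.94 kg, SD 0.55 kg and 12.1% LBW. Cutting the tail to 2% gives a mean of 3.01 kg and 8.3% LBW. A low tail is not foreign to this plan: the Background links STIs to prematurity, and section 11.1.2 counts abortions and stillbirths among the recorded outcomes. One therefore cannot say, without a distributional assumption, that a row must be wrong. But the example needs 6% of babies averaging 1.3 kg. Its treated SD falls to about 0.43 kg, so the birth-weight row would need about 792 per arm, not 970.

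**The 70 g and the 30% have different bases.** The prose ties 70 g to adding SP to nets, and gives the 30% for SP+AZ with possible STI benefit. An effect concentrated in the smallest babies would also cut LBW by more than a uniform shift. Both points soften the treatment-effect mismatch, although Table 3 prints 3.01 kg in the AZ-SP column. Neither touches the control arm: 12% v about 21%.

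**The primary power is unaffected.** A reader might infer that the true primary power is 57% or 45%. The documents do not support that. Section 11.2 sets N from 12% v 8.4%, never assumes 21.2% v 17.7%, and nowhere says the effect is a uniform 70 g shift. If the birth-weight row is the inaccurate one, the result is merely an overpowered comparison of means.

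**Conclusion.** The point holds under approximate normality, and the table is wrong as written on that assumption. The rows imply SDs of about 0.55 kg and 0.37 kg for one variable. The first gives about 21% control LBW where 12% is printed; the second gives about 450 per arm where 970 is printed. Ordinary skewness or a moderate preterm tail does not close the gap.

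The 1,163 and its stated power stand for 12% v 8.4%. What fails is any inference from the 70 g gain to that power; the 75%, 57% and 45% show how sensitive such an inference is to the SD and the control rate. The documents do not settle which assumption is off. The Background reports 22% LBW in Madang under an earlier regimen; that does not fix this trial's rate, but it means 21% cannot be dismissed as implausible.

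**What to change.** In section 11.2:

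- State the birth-weight SD, its source and the distributional assumption.
- Make the two rows consistent. If the SD is 0.37 kg, restate the birth-weight n as about 450 per arm. If it is 0.55 kg, restate the control LBW rate or the control mean, with the resulting LBW power.
- State that a 30% LBW reduction from 12% corresponds to a uniform shift of about 76 g (SD 0.37 kg) to 112 g (SD 0.55 kg).
- Say whether the 70 g and the 30% are meant as one effect, and whether the 70 g refers to SP or to SP+AZ.

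Leave N unchanged. The cost is restated planning figures, one of them possibly less favourable, with no change to enrolment or procedures.

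### Section 11.2 allows for 20% loss as 1163 x 1.2, which leaves 1117 evaluable women per arm rather than 1163; 1163 is not the stated Poisson result; and 11.2 and 11.4.1 name different primary models

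*Combined protocol and SAP*

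**What the plan says.** All references are to the combined protocol and SAP.

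- **Design values (11.2, Table 3).** The calculations are described as "using appropriate two sided tests, a significance level of 5% and a power of 80"%. On the control rate: "If ITNs decrease LBW by 25% then we will expect 12% of babies to be LBW". On the effect: "Our conservative estimate is that SP + AZ will decrease LBW prevalence by 30"%, so 12% falls to 8.4%. Table 3 gives 1163 women per arm for this comparison.
- **Method (11.2).** "we are using an approximate sample size calculation based on comparison of two Poisson rates".
- **Loss (11.2).** "Assuming, a loss of 20% during follow-up, we will thus enroll 1396 women per arm". Section 11.3 repeats the total of 2792 and an expected loss of about 20%.
- **Primary model.** Section 11.2: "The analyses for this primary outcome measure will use Poisson regression (with or without random effects"). Section 11.4.1: "The analyses for the primary outcome measures will use logistic regression". Section 11.1.2 speaks of a difference in proportions.
- **Histology (11.2).** With a usable placental specimen expected from 60% of enrolled women, "the chosen sample size is sufficient to detect a 29% reduction in prevalence of malaria histology".

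**The concern.** The sample-size statement should let a reader go from the design values to the number required, and from there to the number enrolled. Neither step works as written. The named method does not give 1163, and the enrolled number does not leave 1163 after the plan's own loss.

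The two sections also disagree about the primary model, so the protocol does not settle whether the headline result is a rate ratio or an odds ratio. That should be settled before data are compared by arm. Section 11.2 schedules an interim comparison of low birth weight after 1400 deliveries, and section 6.3.3 has the principal investigators holding the treatment code. At stake are a correct statement of power for the primary outcome and a single pre-specified primary analysis.

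**Working it through.** **Inputs**, all from 11.2: p1 = 0.12, p2 = 0.084, d = 0.036, two-sided 5% (z = 1.960), 80% power (z = 0.8416), loss 20%, 1396 enrolled per arm. The sum of the z values squared is 7.849.

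**1. Reproducing 1163**

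- Pooled two-proportion formula, with mean rate 0.102: n = [1.960 x sqrt(2 x 0.102 x 0.898) + 0.8416 x sqrt(0.12 x 0.88 + 0.084 x 0.916)]^2 / 0.036^2 = 1108.3.
- With continuity correction: (1108.3/4) x [1 + sqrt(1 + 4/(1108.3 x 0.036))]^2 = **1163.2**. This matches the plan.
- Two Poisson rates: 7.849 x (0.12 + 0.084)/0.036^2 = **1235.5**.
- Two Poisson rates, square-root scale: 7.849 / [2 x (sqrt 0.12 - sqrt 0.084)^2] = **1225.8**.

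Other two-sided Poisson variants give 1224 (conditional on total events) and 1249 (log rate ratio). None gives 1163 at the stated rates. The STI row of Table 3 (30% against 10%, n = 72) also fits the continuity-corrected formula, which gives 71.2, rounded up to 72.

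**2. Loss allowance**

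- Plan: 1163 x 1.2 = 1395.6, rounded to 1396.
- Left after 20% loss: 1396 x 0.8 = 1116.8, or 1117, and 1163 - 1117 = 46 short.
- Needed to keep 1163: 1163/0.8 = 1453.75, or 1454 per arm.
- Largest loss that still leaves 1163: 1 - 1163/1396 = 16.7%.

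**3. Power at 1117 per arm**

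The null standard error is sqrt(2 x 0.102 x 0.898/1117) = 0.01281. The alternative standard error is sqrt(0.1825/1117) = 0.01278.

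| Basis | Normal deviate | Power at 1117 | Power at 1163 |
| --- | --- | --- | --- |
| Two proportions, uncorrected | (0.036 - 1.960 x 0.01281)/0.01278 | 80.3% | 81.9% |
| Log-odds Wald (log OR 0.397, SE 0.1418 at 1117) | 0.397/0.1418 - 1.960 | 79.9% | not needed |
| Two proportions, continuity-corrected | (0.036 - 1/1117 - 1.960 x 0.01281)/0.01278 | 78.3% | 80.0% |
| Two Poisson rates | 0.036/sqrt(0.204/1117) - 1.960 | 75.9% | 77.6% |

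**4. Model-based Poisson variance on a yes/no outcome**

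The Poisson standard error of the log ratio is proportional to sqrt(1/0.12 + 1/0.084). The binomial one is proportional to sqrt(0.88/0.12 + 0.916/0.084). Their ratio is 1.05, so without a robust variance the Poisson standard error is about 5% too large.

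**5. Histology**

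0.60 x 1396 = 837.6, about 838 per arm. Solving each formula for the rate detectable from 30% with 80% power:

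- two proportions: about 23.9%, a 20.2% reduction (20.6% with continuity correction);
- two Poisson rates: about 23.0%, a 23.5% reduction.

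If the 60% applied only to women left after loss (0.60 x 1117 = 670), the range would be about 22.5% to 26%. None of these is 29%.

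**The case against.** The strongest reply is that the 80% claim survives on the analysis most likely to be run. Section 11.4.1, the analysis plan proper, names logistic regression. The uncorrected two-proportion formula needs 1109 evaluable women, and 1109/0.8 = 1387, which 1396 covers. The loss figure is also a rough assumption: section 11.3 says about 20% and expects more than 90% attendance at each time point. All of this stands. It limits the consequence without making the loss step or the method label correct.

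Four stronger readings are tempting, and the documents do not support them.

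- **The trial is materially underpowered and must enrol more women.** This does not follow. Power after 20% loss is about 80% on a basis close to the unadjusted logistic model. The 75.9% applies only to a plain Poisson comparison, which 11.4.1 does not plan.
- **The model has been left open so that it can be chosen after seeing results.** The documents do not show this. Section 11.4.1 names one model, and 11.2 mentions Poisson while justifying an approximate calculation. It is a contradiction to reconcile.
- **The 389 in the 30% against 20% rows is wrong.** The square-root Poisson formula gives 388.5, so 389 fits the stated method, and it does not determine enrolment.
- **An odds ratio is the wrong effect measure.** Planning on a 30% relative reduction and reporting an odds ratio is a choice. The fault is only that the protocol does not make one choice consistently.

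On histology, a sample that can detect a smaller reduction can also detect 29%, so the statement is conservative and supports no claim of a power shortfall.

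**Conclusion.** The concern holds as a should-fix. Section 11.2 multiplies by 1.2 where it should divide by 0.8, so its own loss assumption leaves 1117 evaluable per arm, 46 below the number it calls required. That is arithmetic on the plan's own figures.

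The figure 1163 does not follow from two Poisson rates at 12% and 8.4%. That it came from the continuity-corrected two-proportion formula is an inference from an exact numerical match, since the documents do not print the formula. A Poisson calculation at 8.3% would give 1163.9, but 8.3% appears nowhere in the plan, and 12% x 0.7 is 8.4%.

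The power cost of the loss error is under 2 points on the continuity-corrected basis (80.0% to 78.3%). Power is about 4 points below 80% on the stated Poisson basis, and there is essentially no shortfall for an uncorrected or log-odds test (80.3% and 79.9%). These figures assume 20% loss in both arms, the planned event rates and no covariate adjustment.

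The conflict between Poisson regression in 11.2 and logistic regression in 11.4.1 is plain on the page. The 29% histology figure is a minor secondary point.

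**What to change.** 1. Keep 2792. In 11.2, state that 20% loss leaves 1117 evaluable women per arm, and give the power at 1117 under the test actually named: about 80% for the unadjusted logistic analysis, 78.3% with a continuity correction, or 75.9% for two Poisson rates.
2. State the formula used for 1163, and remove the Poisson description from that row if it does not apply.
3. Name one primary model and one effect measure, in the same words in 11.2 and 11.4.1, before the interim comparison. If Poisson regression is kept, specify a robust (sandwich) variance.
4. Restate the histology figure for 838 specimens per arm: about 20% to 21% by two proportions, or 23.5% by Poisson, naming the method.

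The cost is a few restated figures and one aligned sentence on the model. No extra women are needed, and the stated power becomes slightly less favourable on two of the three bases. Holding 1163 evaluable under 20% loss would instead take 1454 per arm, which is 58 more per arm and 116 in total. The size of the shortfall does not require that.

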## Participant Enrolment and Follow-Up

This study will enrol 2792 pregnant women over a period of 18-24 months. Enrolment and follow up will occur through Hospital and Health Centre Antenatal Clinics. Apart from some ultrasound visits (particularly at enrolment), no additional study visits will be required, beyond visits for standard antenatal care.

Currently there are high levels of ANC attendance in Madang. If women miss a treatment or follow-up visit they will be visited on the next day by a village reporter and encouraged to visit the health centre or the hospital ANC. We therefore expect >90% attendance at any follow-up time point.

However, people in the study areas do occasionally move the village of residence. In addition some people do grow tired of participating in intensive longitudinal follow up studies and withdraw consent for continued participation.

Women that missed more than 2 treatments will be excluded from all analyses except those on drug side effects. Consequently, we expect about 20% loss of follow-up.

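### Section 11.2 multiplies the 20% loss allowance on instead of dividing it out, so 1396 per arm leaves about 1117 evaluable women against the stated 1163 (minor)

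*Combined protocol and SAP*

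**What the plan says.** Section 11.2 (Sample Size Considerations) sets the primary comparison in Table 3 at LBW of 12% in controls and 8.4% on SP+AZ, "using appropriate two sided tests, a significance level of 5% and a power of 80"%. The text under the table gives the requirement: "a sample size of 1,163 and 970 women per arm, respectively, are required to find a 30% reduction in LBW". The 970 refers to mean birth weight, so LBW drives the size. The next step is the allowance for loss: "Assuming, a loss of 20% during follow-up, we will thus enroll 1396 women per arm".

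Section 11.3 (Participant Enrolment and Follow-Up) gives the total as 2792, which is 2 x 1396. After describing moves, withdrawals and exclusions for missed treatments, it concludes: "Consequently, we expect about 20% loss of follow-up". The total of 2792 also appears in the synopsis and in Section 5.1.

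**The concern.** A loss during follow-up is a fraction of the women enrolled. To finish with 1163 evaluable women after losing 20% of those enrolled, enrolment has to be 1163 divided by 0.80. Adding 20% of 1163 to 1163 gives a smaller number, and removing 20% of that number does not return 1163. As written, the requirement (1163), the expected loss (20%) and the enrolment (1396) cannot all be true.

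The sentence in question fixes enrolment for the primary outcome. What is at stake is whether the stated 80% power is delivered at the loss the plan itself expects.

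**Working it through.** **Inputs, all from Section 11.2 unless noted.** Two-sided 5% significance; 80% power; control LBW 12% ("If ITNs decrease LBW by 25% then we will expect 12% of babies to be LBW"); a 30% relative reduction ("Our conservative estimate is that SP + AZ will decrease LBW prevalence by 30"%), hence 0.12 x 0.70 = 8.4%; 1163 required per arm; 20% loss (repeated in 11.3); 1396 enrolled per arm.

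**1. Reproduce 1163.** With p1 = 0.12, p2 = 0.084, difference d = 0.036 and mean p = 0.102, the uncorrected two-proportion size is

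n = [1.960 x sqrt(2 x 0.102 x 0.898) + 0.842 x sqrt(0.12 x 0.88 + 0.084 x 0.916)]² / 0.036² = 1108.3.

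With the continuity correction,

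n' = (n/4) x [1 + sqrt(1 + 4/(n x d))]² = 1163.2.

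This matches the plan's 1163. Section 11.2 names a comparison of two Poisson rates instead, but variants of that method give about 1226 to 1249. The continuity-corrected formula is therefore inferred from the match; the plan does not name it.

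**2. Reproduce 1396.** 1163 x 1.20 = 1395.6, rounded up to 1396. The loss was multiplied on.

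**3. Apply the plan's own loss.** 1396 x 0.80 = 1116.8, about 1117 per arm. Shortfall: 1163 - 1117 = 46 per arm, and 46/1163 = 4.0%.

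**4. Divide the loss out.** 1163/0.80 = 1453.75, rounded up to 1454 per arm, or 2908 in total. That is 58 more per arm and 116 more in total than planned.

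**5. Loss that 1396 can absorb.** 1 - 1163/1396 = 16.7%.

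**6. Power for 12% v 8.4%.** The corrected power is

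Φ{[(d - 1/n) - 1.960 x sqrt(2 x 0.102 x 0.898/n)] / sqrt[(0.12 x 0.88 + 0.084 x 0.916)/n]}.

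The uncorrected version drops the 1/n. The Poisson version is Φ{0.036/sqrt(0.204/n) - 1.960}.

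| Method | 1163 per arm | 1117 per arm | Change (points) |
|---|---|---|---|
| Two proportions, continuity-corrected (reproduces 1163) | 80.0% | 78.3% | -1.7 |
| Two proportions, uncorrected | 81.9% | 80.3% | -1.6 |
| Two Poisson rates (named in 11.2) | 77.6% | 75.9% | -1.7 |

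The last column is the effect of the inflation error. In the Poisson row, power is already below 80% at the full 1163, because 1163 is not a two-Poisson-rates number. That is a separate issue.

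**The case against.** **Loss may be lower than 20%.** Section 11.3 expects more than 90% attendance at any follow-up point, calls the 20% approximate, and derives it partly from excluding women with missed treatments. Babies born at home are to be traced and weighed within 7 days. At 10% loss, 1396 leaves 1396 x 0.90 = 1256, comfortably above 1163. This stands as a reason why the shortfall may not occur. It does not repair the sentence, because the plan still settles on about 20% in both sections and gives no other derivation of 1396.

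**The uncorrected test still has 80.3% power at 1117.** This is true, and Section 11.4.1 plans logistic regression, not a continuity-corrected test. It shows how little is at stake. But the plan did not arrive at 1163 that way, since the uncorrected size is 1109. Adopting that formula now because it clears 80% would be choosing it after seeing the answer.

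**Two stronger readings should be resisted.**

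- A reader might infer that the authors themselves worked with 1117, because Section 11.2 also claims a "0.26g/dl increase in maternal Hb with a power of 80"%. Table 3's 845 per arm for a 0.3 g/dl difference implies an SD of sqrt(845 x 0.3²/(2 x 7.849)) = 2.20. The detectable difference is then 0.261 at 1117 and 0.256 at 1163. Both round to 0.26, so the figure cannot tell them apart. The claim in the same sentence about STIs falling from 25% to 20% leans the other way, if anything: by the corrected formula it needs 1134 per arm, which 1163 meets and 1117 does not. Uncorrected it needs 1094, which both meet.
- A reader might take the 76% Poisson figure as the damage done by the error. Only 1.7 points of it are.

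**Conclusion.** The sentence is wrong as written, and the error is minor. At the plan's own 20% loss, 1396 enrolled per arm gives about 1117 evaluable, 46 per arm short of the stated 1163, and the stated 80% power becomes 78.3% by the formula that reproduces 1163.

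This rests on reading the 20% as a fraction of enrolled women, which is how Section 11.3 describes it, and on the plan's 12% and 8.4%. The shortfall itself does not depend on which power formula is used; only the power figure does. A deficit of less than 2 points is small beside the uncertainty in the assumed control rate and effect. It changes neither the planned analysis nor the validity of the trial, and the documents do not support calling the trial materially underpowered on this ground.

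**What to change.** Keep 2792 and correct the sentence in Section 11.2 in one of two ways:

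- *With 20% loss, 1396 enrolled per arm gives about 1117 evaluable per arm; power for LBW of 12% v 8.4% is about 78% (two-sided 5%, continuity-corrected).*
- *Enrolment of 1396 per arm gives 80% power for LBW of 12% v 8.4% only if loss is at most 16.7%.* Section 11.3 would then need to be reconciled with that loss.

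The cost is one sentence and a slightly less favourable power statement; no extra women are needed. If the sponsor prefers to retain 80% at 20% loss on the formula behind 1163, enrolment would be 1454 per arm (2908 in total, 116 more). For a gain of under 2 points I would not press for that.
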